### Sample size determination

Sample size consideration for this study is based on the precision of the survival estimate for the outcome progression-free survival. Based on previous results with the combination of Irinotecan and 5-FU therapy in patients with biliary tract cancers we assume a median survival time of 3 months. Assuming an exponential failure time with a median survival of 3 months (hazard rate: 0.23 per month) and a censoring rate of 0.04 per month, a total sample size of 28 patients (including 3 calculated drop outs and invalid cases) results in an expected standard error of 0.09 for the 3 months survival.

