**2. Endpoints**
**2.1 Primary Endpoint** • Median progression free survival (PFS) assessed by the local investigator

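### The stated standard error of 0.09 for 3-month PFS does not follow from the plan's own inputs, which give about 0.10; a minor correction of a printed figure

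*Protocol article*

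**What the plan says.** Under *Sample size determination*, the protocol article rests the number of patients on the precision of the PFS estimate. It gives all the ingredients:

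- Event times: "Assuming an exponential failure time with a median survival of 3 months (hazard rate: 0.23 per month" (closing bracket omitted).
- Losses: "a censoring rate of 0.04 per month".
- Result: "a total sample size of 28 patients (including 3 calculated drop outs and invalid cases) results in an expected standard error of 0.09", the standard error being that of survival at 3 months.

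*Statistical considerations* fixes the method: Turnbull's non-parametric survival estimate, Greenwood variance, and confidence intervals on the log scale. *Methods/study design* repeats the total of 28, including the 3 expected losses, and calls the trial exploratory, phase IIA and single-arm. Table 1 gives the primary endpoint as "Median progression free survival (PFS) assessed by the local investigator".

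**The concern.** The plan has no hypothesis test, power statement or target effect. The standard error of 0.09 is therefore the only quantitative support for enrolling 28 patients. It is printed next to every input needed to derive it, so it can be checked directly and does not depend on a fuller protocol or a statistical analysis plan.

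A quick look already raises doubt. Survival at 3 months is 0.50 by assumption. A plain binomial proportion of 0.50 in 28 fully observed patients has a standard error of 0.0945. Censoring can only increase that, and so can losing patients altogether. The plan includes both, yet states a figure at or below the ideal case. If the figure is too small, a reader will expect a somewhat tighter PFS estimate than the design can deliver.

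**Working it through.** **Inputs** (all from *Sample size determination*, except the variance method and interval scale, which are from *Statistical considerations*)

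- Median 3 months, so S(3) = 0.50 and hazard h = ln 2 / 3 = 0.2310 per month. The printed 0.23 agrees.
- Censoring c = 0.04 per month, taken here as an exponential censoring hazard.
- t = 3 months.
- n = 28 if all enrolled patients are analysed; n = 28 − 3 = 25 if the 3 losses contribute nothing.

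**Trying to reproduce 0.09**

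With no censoring and n = 28: √(0.25/28) = 0.0945, which rounds to 0.09. With no censoring and n = 25: √(0.25/25) = 0.100. So 0.09 is reached on the planned type of estimator if the stated censoring is dropped and all 28 are counted as fully observed.

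**Using the stated inputs**

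Under exponential events and exponential censoring, the large-sample Greenwood variance is

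Var = [S(t)² / n] × [h / (h + c)] × [exp((h + c)t) − 1].

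- h + c = 0.2710; (h + c)t = 0.8131; exp(0.8131) − 1 = 1.255.
- h / (h + c) = 0.8524.
- Variance for one patient: 0.25 × 0.8524 × 1.255 = 0.2674.

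| Patients analysed | Formula SE | Simulated SD of the estimate | Simulated mean Greenwood SE |
|---|---|---|---|
| 28 | √(0.2674/28) = 0.0977 | 0.0975 | 0.0959 |
| 25 | √(0.2674/25) = 0.1034 | 0.1035 | 0.1012 |

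The simulation used 100,000 trials per row, with exactly observed event times. Using h = 0.23 instead of ln 2 / 3 leaves the formula values unchanged to four decimals.

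**Other ways of allowing for censoring** (28 / 25 patients)

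- Actuarial adjustment: 0.097 / 0.103.
- Effective sample size: 0.100 / 0.106.
- 4% lost in total rather than per month: 0.096 / 0.102.

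None rounds to 0.09.

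**Size of the gap**

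- n = 28: 0.0959/0.09 = 1.07 to 0.0977/0.09 = 1.09, so 7-9% larger.
- n = 25: 0.1012/0.09 = 1.12 to 0.1034/0.09 = 1.15, so 12-15% larger.
- At these inputs an SE of 0.09 needs 0.2674/0.09² ≈ 33 analysed patients. An SE that only rounds to 0.09 needs 0.2674/0.095² = 29.6, so 30.

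**Effect on the planned interval** (log scale, 0.50 × exp(±1.96 × SE/0.50))

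- SE 0.09: 0.35 to 0.71.
- SE 0.0977 (28 patients): 0.34 to 0.73.
- SE 0.1034 (25 patients): 0.33 to 0.75.

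**The case against.** Several points against the concern have force.

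*The gap is small and nothing depends on it.* This stands. The interval limits move by 0.01 to 0.04, and the article names no threshold or target precision that would be missed.

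*An expected standard error is, read literally, the mean Greenwood value.* That is 0.096 with 28 patients, about 0.001 from rounding to 0.09. This is fair and is why a range is given, but 0.096 still rounds to 0.10.

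*The 25 is an inference.* This also stands. The plan attaches its figure to the total of 28 and never says that 25 are analysed. Drop-outs with some follow-up are censored observations, and the 0.04 per month may already represent them. Removing 3 patients and also applying that rate could count the same losses twice. The 0.103 is therefore conditional, but the result with 28 does not depend on it.

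*There are other routes to 0.09.* A reader might infer that the authors must have ignored censoring. The documents do not show this. Cutting 0.0977 to two decimals gives 0.09. A parametric exponential estimate that keeps the stated censoring gives 0.087 (28 patients) or 0.092 (25) at 4 months of follow-up, and *Study duration* expects about 4 months of treatment. These routes may explain the figure, but they do not justify it: truncation understates the standard error, and the planned estimator is non-parametric.

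*The precision is for the 3-month rate, whereas the primary endpoint is the median.* A reader might call this a second error. It is not one: 3 months is the assumed median, so the standard error of S(3) is the precision at the point from which the median's interval is read. A separate interval for the median would be helpful but is optional.

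**Conclusion.** The printed standard error of 0.09 is not what the plan's inputs and method give. The correct figure is about 0.10: 0.098 (mean Greenwood 0.096) with all 28 analysed, and 0.103 (0.101) on condition that the 3 losses contribute no data. Precision is overstated modestly, and the severity is low.

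This rests on reading the censoring rate as an exponential hazard and on exactly known progression times. The alternative treatments of censoring shown above do not change the conclusion. Turnbull estimation from interval-censored assessments would not be expected to do better than this calculation; how much worse is not quantified here.

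A reader might infer that the trial is too small or must enrol more patients. The documents do not support that: no precision requirement is set, and about 0.10 can serve an exploratory trial as well as 0.09. How the authors arrived at 0.09 cannot be determined from the article.

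**What to change.** Keep 28 patients and correct the sentence under *Sample size determination*. Suggested wording: *expected standard error about 0.10 for 3-month PFS (0.098 with 28 patients analysed; 0.103 if only 25 are evaluable), corresponding to a log-scale 95% confidence interval around 0.50 of about 0.34-0.73 or 0.33-0.75 respectively*. Quote the interval limits rather than a symmetric half-width, because the plan specifies log-transformed intervals.

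It would help to say whether the 3 drop-outs and invalid cases are separate from the losses covered by the 0.04 per month, since that decides which figure applies.

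Optionally, add the expected precision of median PFS. Dividing the standard error by the density at the median (0.231 × 0.50 = 0.1155) gives roughly 0.85 months with 28 patients and 0.90 months with 25.

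The cost is wording only: one stated figure becomes slightly less favourable, with no extra patients and no change to the analysis.

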### Assessment of severity/intensity of adverse events

The severity of any (S)AE's occurring will be assessed using the National Cancer Institute Common Terminology Criteria for Adverse Events (NCI-CTCAE), version 5.0.

Personnel of the trial center that is involved with the study must have access to a copy of the NCI-CTCAE version 5.0.

AE's are to be documented with the following details:

Indication of the diagnosis or syndrome, duration of the AE, severity, assessment of whether an AE is serious or not (if an AE is to be classified as a SAE, additional reporting as SAE is required), assessment of the causal relationship with the study medication and the outcome of the AE's.In this study, all adverse events occurring from the time of signed informed consent by the patient until 30 days after the last administration of the study medication are to be documented as adverse events.A serious adverse event (SAE) or serious adverse drug reaction (SADR) is any AE that fulfils at least one of the following criteria: results in death, is life-threatening, requires inpatient hospitalization or prolongation of existing hospitalization, is a congenital anomaly/birth defect or constitutes an important medical event.Important medical events are defined as those occurrences that may not be immediately life threatening or result in death, hospitalization, or disability, but may jeopardize the subject or require medical or surgical intervention to prevent one of the other outcomes listed above. Medical and scientific judgment should be exercised in deciding whether such an AE should be considered serious. SAE’s must be reported immediately within 24 h knowledge of the event.

### Translational research

It is intended to collect plasma and serum samples from all patients, following separate declaration of consent. Samples are to be taken at baseline, at each restaging visit and at the end of the treatment visit. After centrifugation, the serum and plasma have to be stored at -80° Celsius for further analyses. The aim is to measure concentrations of inflammatory cytokines using FACS bead technology in the serum of patients. This panel will include analysis of Osteopontin, suPAR, APRIL, TWEAK, TRAIL, CCL1, 2, 5, and CXCR1, 2, 5, 9, which all have been demonstrated being regulated in the serum of patients with gastrointestinal cancers. Moreover concentrations of circulating miRNAs and lncRNAs will be measured in these samples. The ultimate aim of these retrospective analyses is to study the predictive value with regard to response, survival periods and development of resistance.

Liquid biopsies will be taken to perform translational research on cell-free DNA in blood, following separate declaration of consent. cfDNA exome sequencing will be performed using a panel of 28 mutations (e.g. IDH1, IDH2, SMAD4). These mutations will be recapitulated in patients´ serum by using cfDNA exome sequencing and correlated with clinical response, survival and development of resistance.

Stool analyses will be collected at baseline, at each restaging visit and at the end of the study treatment, following separate declaration of consent. In order to analyze the gut macrobiota we will perform different molecular-genetic examinations. First stool DNA will be prepared and bacterial gene sequences coding for 16S RNA will be quantified. As a screening examination a quantitative PCR using group-specific primer against variable parts of bacterial 16S RNA will be used. Next we will use a defined panel of 15 primer-pairs against the most prominent species of the gut microbiota to analyze rifaximin dependent alterations. Moreover it is planned to apply the highly innovative high-throughput sequencing of bacterial 16S RNA for complete and unbiased analysis of the gut microbiota.

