**Safety** **• Type, frequency and severity of adverse events with severity according to NCI CTCAE version**
**Health-Related Quality of Life** • HR-QoL according to EORTC QLQ-C30 and the EQ-5D-5L
**Translational part** • **cfDNA exome sequencing**: a panel of 28 mutations (e.g. IDH1, IDH2, SMAD4) that are specific for BTC will be recapitulated in patient’s serum by using cfDNA exome sequencing. • **Circulating miRNAs and lncRNAs**: Alterations in serum miRNAs as prognostic markers will be analysed using array based techniques in representative patients and significantly altered miRNAs will be validated using qPCR in the whole cohort of patients. • Concentrations of inflammatory cytokines: A panel of inflammatory cytokines will be analyzed using FACS bead technology in the serum of patients. This panel will include analysis of Osteopontin, suPAR, APRIL, TWEAK, TRAIL, CCL1, 2, 5, and CXCR1, 2, 5, 9) • **Gut microbiome analysis:** By using high-throughput sequencing of bacterial 16S RNA a complete and unbiased analysis of the gut microbiota will be performed in each individual patient. Both the baseline composition and alterations during therapy will be correlated with PFS and response to therapy.

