#### Dose modification of FTD/TPI

A maximum of 1 dose reduction level (20 mg/m^2^ BSA BID) is permitted for FTD/TPI. Table 3 displays the dose in mg to be taken twice daily calculated per m^2^ BSA. (Tables 4 and 5).

**Table 3 Tab3:** Calculation of dose reduction for FTD/TPI in mg according to BSA used in the TRITICC trial

**Starting dose** **20 mg/m**^**2**^	**BSA (m**^**2**^**)**	**Dose in mg** **2 × daily**	**Tablets per dose**		**Total daily dose (mg)**
			**15 mg**	**20 mg**	
	< 1.14	20	0	1	40
	1.15 – 1.34	25!	2!	1!	50!
	1.35 – 1.59	30	2	0	60
	1.60 – 1.94	35	1	1	70
	1.95 – 2.09	40	0	2	80
	2.10 – 2.34	45	3	0	90
	> 2.35	50	2	1	100

(!) At a total daily dose of 50 mg, patients should take 1 × 20 mg tablet in the morning and 2 × 15 mg tablets in the evening

**Table 4 Tab4:** Dose interruption and resumption criteria for haematological toxicities related to myelosuppression [21]

**Parameter**	**Interruption**	**Resumption criteria**^**a**^
Neutrophils	< 0.5 × 10^9^/L	< 1.5 × 10^9^/L
Platelets	< 50 × 10^9^/L	> 75 × 10^9^/L

^a^Resumption criteria applied to the start of the next cycle for all patients regardless of whether or not the interruption criteria were met

**Table 5 Tab5:** Recommended dose modifications for FTF/TPI in case of haematological and non-haematological adverse reactions [21]

**Adverse reaction**	**Recommended dose modifications**
• Febrile neutropenia	• Interrupt dosing until toxicity resolves to Grade 1 or baseline
• Grade 4 neutropenia (< 0.5 × 10^9^/L) or thrombocytopenia (< 25 × 10^9^/L) that results in more than 1 week’s delay in start of next cycle	• When resuming dosing, decrease the dose level by 5 mg/m^2^/dose from the previous dose level
• CTCAE version 4 non-haematologic Grade 3 or Grade 4 adverse reaction; except for Grade 3 nausea and/or vomiting controlled by antiemetic therapy or diarrhoea responsive to antidiarrhoeal medicinal products	• Dose reductions are permitted to a minimum dose of 20 mg/m^2^/dose BID daily • Do not increase dose after it has been reduced

Dose escalation of FTD/TPI is not permitted after it has been reduced.

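### Serum CCL5 is confounded by platelet count, although plasma is banked at the same visits and could be used instead

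*Protocol article*

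**What the plan says.** Two places in the protocol article fix the matrix. Table 1, translational part: "A panel of inflammatory cytokines will be analyzed using FACS bead technology in the serum of patients". Section Translational research: "The aim is to measure concentrations of inflammatory cytokines using FACS bead technology in the serum of patients". The latter section lists the analytes: "This panel will include analysis of Osteopontin, suPAR, APRIL, TWEAK, TRAIL, CCL1, 2, 5, and CXCR1, 2, 5, 9".

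Plasma is available as well: "It is intended to collect plasma and serum samples from all patients, following separate declaration of consent", and after centrifugation "the serum and plasma have to be stored at -80° Celsius for further analyses". The timing is serial: "Samples are to be taken at baseline, at each restaging visit and at the end of the treatment visit". The section states that the purpose is to study predictive value for response, survival and resistance. Its only support for serum is that these markers are reported as regulated in the serum of patients with gastrointestinal cancers.

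Platelet falls on treatment are anticipated. Table 4, in the section Dose modification of FTD/TPI, is titled "Dose interruption and resumption criteria for haematological toxicities related to myelosuppression" and has a platelet row (interruption below 50, resumption above 75 × 10^9/L). Table 5 names thrombocytopenia as a ground for dose modification. The inclusion criteria admit patients from 100 × 10^9/L, with no upper limit.

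**The concern.** Blood has to clot in the tube to give serum. Clotting activates platelets, which store CCL5 and release it. It also generates thrombin, which cleaves osteopontin. This is general laboratory knowledge; the article neither states nor contradicts it. Serum CCL5 is therefore the sum of what circulated in the patient and what platelets released after the draw, and the second part rises and falls with the platelet count.

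Two readings of the data are at risk. At baseline, an association of serum CCL5 with response or survival could partly be an association with platelet count. On treatment, serum CCL5 can fall because the study drugs lower platelets, with no change in circulating CCL5, and the fall could be taken for an inflammatory response or a resistance marker. Because the article states the matrix twice, this is a choice it makes and not a detail left to a laboratory manual.

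**Working it through.** The article gives no figure on this point, so there is nothing of its own to reproduce. The check has a documentary part and an illustrative part.

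**Documentary part.** Both places that name a matrix for the panel name serum. CCL5 and osteopontin are on the panel. Plasma is banked but given no role in this assay. Samples are drawn at baseline and again during treatment, and the regimen is expected to lower platelets. All five elements stand in the text.

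**Size of the artefact.** Assumptions, none of them in the article:
- s = share of serum CCL5 released by platelets in the tube, 0.5 to 0.95.
- That share is proportional to platelet count.
- Circulating CCL5 does not change.
- d = fractional platelet fall, either 25% or 60% (for example 250 to 100 × 10^9/L).

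Formula: serum ratio = (1 − s) + s × (1 − d), so the apparent fall is s × d.

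| s | d = 0.25 | d = 0.60 |
|---|---|---|
| 0.5 | 12.5% | 30% |
| 0.8 | 20% | 48% |
| 0.95 | 23.75% | 57% |

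The last column also describes a baseline contrast. Two eligible patients with equal circulating CCL5 and platelets of 250 and 100 × 10^9/L (the latter being the entry limit) would differ in serum CCL5 by 30% to 57%.

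**How far serum CCL5 reflects circulating CCL5.** Further assumptions: circulating CCL5 and platelets are independent and lognormal with mean 1, with log-SDs of 0.5 and 0.4. Their SDs are then √(e^0.25 − 1) = 0.533 and √(e^0.16 − 1) = 0.417. With serum = (1 − s) × circulating + s × platelets, the correlation with circulating CCL5 is (1 − s) × 0.533 / √{[(1 − s) × 0.533]² + [s × 0.417]²}. The correlation with platelets has s × 0.417 in the numerator.

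| s | with circulating CCL5 | with platelets |
|---|---|---|
| 0.25 | 0.97 | 0.25 |
| 0.5 | 0.79 | 0.62 |
| 0.8 | 0.30 | 0.95 |
| 0.95 | 0.07 | 1.00 |

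On the log scale the values for s = 0.5, 0.8 and 0.95 are 0.75, 0.31 and 0.07 with circulating CCL5, and 0.63, 0.94 and about 1.0 with platelets. The two correlations are equal at s = 0.533 / (0.533 + 0.417) = 0.56. Below that share the circulating signal is the stronger component; above it, platelets are.

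**Osteopontin.** No calculation is possible. The article does not say whether the bead assay reads intact or cleaved protein, so neither the size nor the direction of a bias can be derived.

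**The case against.** The strongest case against has five parts.

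1. **The mechanism and its size come from outside the article.** The platelet-derived share, the platelet fall and the SDs are all assumed. This stands as a limit on size. It does not remove the qualitative point, because release of platelet contents on clotting is basic to how serum is made.

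2. **Platelet dominance is put into the model, not found by it.** This also stands. A reader might infer that serum CCL5 mainly measures platelets and says little about circulating inflammation. At s = 0.5 the circulating signal is still the stronger component (0.79 against 0.62, or 0.75 against 0.63 on the log scale). The stronger reading needs a share above about 0.56 under the assumed SDs, and nothing in the article establishes that.

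3. **Platelet counts at sampling are unknown.** Table 4 gives management thresholds, not expected counts. Its footnote applies the resumption criteria at the start of the next cycle for all patients, and the article does not give the position of restaging within the cycle. The 60% fall is therefore an example, and the 25% fall is shown beside it.

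4. **A change-from-baseline analysis of cytokines is not stated.** The article speaks of alterations during therapy only for the gut microbiome. For cytokines, such an analysis is an inference from the serial sampling and the resistance aim. The baseline confounding does not depend on it.

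5. **Serum is the matrix of the earlier evidence.** That is a real reason, and changing matrix costs comparability. But a difference seen in serum could itself reflect platelets, and earlier serum findings do not address serial sampling under myelosuppressive drugs.

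**Conclusion.** The concern holds as confounding, not as replacement of the signal. Measuring CCL5 in serum mixes circulating CCL5 with an amount that depends on platelet count, both between patients at baseline and within patients on treatment. For assumed shares of 0.5 to 0.95, the apparent fall is about 12% to 24% for a 25% platelet fall and 30% to 57% for a 60% fall, with circulating CCL5 constant. These figures rest on assumed shares, assumed platelet falls and proportional release. At a share of 0.25 the problem would be slight, since the correlation with circulating CCL5 is still 0.97.

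Osteopontin may be affected, depending on the assay, and no size can be given. A reader might extend the objection to the whole panel; nothing here supports that.

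The consequence is small for the trial as a whole. The panel is a secondary translational endpoint in 28 patients, and the article describes its analysis of secondary outcomes as exploratory. PFS, OS, response and safety are untouched. This is a worthwhile improvement and not a defect that threatens the trial.

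**What to change.** In Table 1 and in the section Translational research, name plasma made platelet-poor by a second spin before freezing as the matrix for CCL5, and preferably for osteopontin. Moving the rest of the panel is optional.

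The timing of the spin matters. Platelets left in single-spun plasma can release CCL5 on freezing and thawing, so a second spin after storage may come too late. The article gives a recruitment start of Q3 2021 and an 18-month recruitment period, and was published in May 2023, so many samples were probably already frozen. It mentions centrifugation without giving the number of spins. For samples frozen after one spin, or where only serum exists, relate CCL5 to outcome with adjustment for the platelet count of the same day, and do not interpret an on-treatment fall as an inflammatory or resistance signal.

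Cost: no new blood draw. It takes a change of aliquot with a short handling note for samples still to be processed, and one covariate for the others. The downside is that plasma results are less directly comparable with earlier serum-based work.

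### The cfDNA mutation analysis is assigned to serum although plasma is collected from the same patients, which lowers sensitivity for low-fraction variants (minor)

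*Protocol article*

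**What the plan says.** All references are to the protocol article.

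- **Table 1, Translational part** lists "a panel of 28 mutations (e.g. IDH1, IDH2, SMAD4) that are specific for BTC" and says they will be looked for in the patient's "serum by using cfDNA exome sequencing".
- **Translational research, cfDNA paragraph** repeats serum as the specimen and states the purpose: "serum by using cfDNA exome sequencing and correlated with clinical response, survival and development of resistance". The same paragraph opens more loosely: "Liquid biopsies will be taken to perform translational research on cell-free DNA in blood". That sentence names neither a tube type nor a schedule.
- **Translational research, first paragraph**: "It is intended to collect plasma and serum samples from all patients, following separate declaration of consent". For these samples the timing is given: "Samples are to be taken at baseline, at each restaging visit and at the end of the treatment visit". Handling is described only as centrifugation and storage at -80 °C. The uses named for them are cytokines, miRNAs and lncRNAs.

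Plasma is never assigned to the cfDNA work, and no reason is given for choosing serum.

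**The concern.** Serum is what remains after blood has clotted. White cells break down during clotting and release ordinary genomic DNA, which carries none of the tumour's mutations. The mutant share of the DNA is therefore lower in serum than in plasma drawn at the same time, and a mutation near the detection limit can be lost. This is general specimen knowledge and is not stated in the article. Its direction is clear; its size here is unknown.

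The mutation results are to be correlated with response, survival and resistance in at most 28 patients. Carriers misclassified as non-carriers weaken those correlations, and a sample of this size has little room for that.

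There is also a conditional concern. If cfDNA is sampled repeatedly and allele fraction is followed over time, the amount of white-cell DNA may differ between samples, because treatment can change the white count. An apparent rise or fall could then occur with no change in the tumour.

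**Working it through.** The plan states no figure on this point, so there is nothing to reproduce. The calculations show direction and range only.

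**1. Sensitivity**

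Inputs, all assumed because the article gives none of them:
- allele fraction in plasma, v: 1% or 5%
- dilution in serum, D: 3-fold or 10-fold (D = 1 stands for plasma)
- reads at the site, n: 1,000
- a mutation is called at 3 or more mutant reads

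Formula: P(detect) = P(X ≥ 3) = 1 − P(0) − P(1) − P(2), with X ~ Binomial(n, v/D).

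| Plasma fraction | Specimen | v/D | Expected mutant reads | P(detect) |
|---|---|---|---|---|
| 1% | plasma | 1.00% | 10.0 | 0.997 |
| 1% | serum, 3-fold | 0.33% | 3.3 | 0.65 |
| 1% | serum, 10-fold | 0.10% | 1.0 | 0.08 |
| 5% | plasma | 5.00% | 50 | 1.00 |
| 5% | serum, 3-fold | 1.67% | 16.7 | 1.00 |
| 5% | serum, 10-fold | 0.50% | 5.0 | 0.88 |

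Worked line (1%, 10-fold): P(0) + P(1) + P(2) = 0.368 + 0.368 + 0.184 = 0.920, so P(detect) = 0.08.

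The result also depends on depth. At an assumed 200 reads, a 5% plasma variant is detected with probability 0.998 in plasma, 0.65 at 3-fold dilution and 0.08 at 10-fold. A 1% variant has 0.32 in plasma, then 0.03 and 0.001. Plasma and serum should be compared at the same depth; setting serum at 200 reads against plasma at 1,000 would mix two separate changes.

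**2. Shift over time (only if cfDNA is serial and allele fraction is the readout)**

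Model: serum fraction = v / (1 + k·w). Here k is clotting-released white-cell DNA relative to plasma cfDNA at baseline, and w is the white count relative to baseline. Total dilution at baseline is 1 + k. Both k and w are assumed; v = 1%.

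| k | w = 1 | w = 0.5 | w = 0.25 | Ratio, w = 0.25 to w = 1 |
|---|---|---|---|---|
| 1 | 0.50% | 0.67% | 0.80% | 1.6 |
| 3 | 0.25% | 0.40% | 0.57% | 2.3 |
| 10 | 0.09% | 0.17% | 0.29% | 3.1 |

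The shift can also go the other way. With k = 3 and a doubled count (w = 2), the fraction is 1%/(1 + 6) = 0.14%, against 0.25% at baseline. In this model plasma has k = 0 and stays at 1% throughout. That is an idealisation, because handling can leave some white-cell DNA in plasma too.

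**3. What the article supports for part 2**

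Myelosuppression is anticipated: Table 4 is titled "Dose interruption and resumption criteria for haematological toxicities related to myelosuppression". The Growth factors section allows G-CSF for febrile neutropenia, which can raise the count. The baseline, restaging and end-of-treatment schedule belongs to the plasma and serum paragraph, not to the liquid biopsies. Allele fraction is not mentioned anywhere.

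**The case against.** The strongest case against has five parts.

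- **Serum may be loose wording**, since the same paragraph also speaks of cell-free DNA in blood. This is possible, but serum is named in both places that describe the assay, and the looser phrase names no specimen. The text would need correcting either way.
- **Every input to the size is assumed.** This stands. At 1,000 reads a 5% variant is barely affected, so the loss could be large or slight, depending on figures the article does not give.
- **Confounding by myelosuppression is not established.** A reader might infer that serum ties the resistance readout to drug toxicity. The documents do not support that as a finding: no serial schedule is stated for the liquid biopsies, no allele-fraction readout is named, nothing says that restaging blood is drawn when counts are low, and G-CSF can push counts up. Only the aim of studying resistance hints at serial reading. It remains a possibility.
- **Exome against panel.** A reader might also infer that reads will be spread over the whole exome instead of the 28 targets. The cfDNA paragraph says the sequencing uses a panel of 28 mutations, which may already mean a targeted assay, so there is no basis for asking that the method be replaced.
- **Plasma may not be ready to use.** This stands in part. Tube type, spin protocol and time to processing are not given, and the cfDNA work is mentioned with its own separate consent. Both need checking before the switch.

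**Conclusion.** The point holds as a minor one. The article twice names serum for cfDNA sequencing while collecting plasma from the same patients, and gives no reason for the choice. Followed as written, this lowers sensitivity for tumour mutations, mainly those at low allele fraction. Under the stated assumptions the loss runs from negligible (5% variant, 3-fold dilution, 1,000 reads) to nearly complete (1% variant, 10-fold dilution). The conclusion rests on the laboratory premise that clotting releases leukocyte DNA; its size in this trial is unknown.

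A drift of the apparent allele fraction with white count is conditional on serial sampling and on that readout being used. The primary PFS analysis, overall survival, response and safety are not touched. The consequence is confined to an exploratory translational secondary endpoint.

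**What to change.** In Table 1 (Translational part) and in the cfDNA paragraph under Translational research, name plasma as the specimen for cfDNA sequencing. First confirm two things: that the plasma is collected and processed in a way suited to cfDNA, and that the separate consent covers sequencing of it. Keep serum for the cytokines.

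Use one specimen type within a patient. Where only serum exists, do not interpret changes in allele fraction over time. If the sponsor prefers serum throughout, state the reason and record the white count at each draw.

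**Cost:** wording in two places and in the laboratory instructions. No new visit is needed, and no new sample if the stored plasma proves suitable. The downside is that plasma yields less total DNA than serum.
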